### Study Endpoints

The primary endpoint is the occurrence of major postoperative complications, defined according to The European Society of Anesthesiology (ESA) and the European Society of Intensive Care Medicine (ESICM) guideline (31) and Society of Thoracic Surgeons (STS) guidelines (32–34) on perioperative outcome measures. Thus we define major postoperative complications as the occurrence of any of the following: (1) acute kidney injury (AKI) stage 2 or more according to the KDIGO definition (35); (2) acute respiratory distress syndrome (ARDS) according to the Berlin definition (36) or respiratory failure (PaO_2_/FiO_2_ <300 mm Hg); (3) stroke, defined as an embolic, thrombotic or hemorrhagic cerebral event with persistent residual motor, sensory or cognitive dysfunction; (4) delirium identified using the Intensive Care Delirium Screening Checklist (37); (5) myocardial infarction: post-surgical myocardial infarction will be screened if serum cardiac biomarker (troponin I) continues to increase after surgery, or decreases and then increases again; and diagnosis will be confirmed if (i) new pathological Q waves appear in different territories than those identified before surgery, or (ii) angiographically documented new native coronary artery occlusion, or (iii) imaging evidence of new loss of viable myocardium or new regional wall motion abnormality (38); (6) circulatory shock for any cause, defined as follows: (i) systolic arterial pressure <90 mm Hg or the mean arterial pressure <70 mm Hg, or blood pressure decreases by >40 mm Hg from baseline, and (ii) clinical signs of tissue hypoperfusion, and iii) serum lactate >2 mmol/L (39); (7) severe sepsis or septic shock according to the Surviving Sepsis Guidelines definition (40); (8) abdominal compartment syndrome: intra-abdominal pressure >20 mm Hg; (9) reoperation; (10) cardiac arrest; (11) death from any cause.

The secondary endpoints include the duration of mechanical ventilation, length of ICU stay, ICU mortality, and hospital mortality. Data will be collected and analyzed from all patients, even if they cannot finish the full-term follow-up (e.g., patients die or withdraw from medical care).

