### Study Setting and Population

The study setting is the cardiac intensive care unit (ICU) (20 beds) and the department of cardiac surgery (118 beds) at a tertiary teaching hospital.

All patients who receive elective cardiac surgery involving cardiopulmonary bypass (CPB) will be screened for study eligibility.

The inclusion criteria are (1) Age ≥ 18; (2) Receive elective cardiac surgery involving CPB; (3) Admitted into ICU after the surgery; (4) With an arterial line and a central venous catheter in place. Exclusion criteria are: (1) Acute or chronic kidney disease prior to surgery (2) Acute or chronic hepatic insufficiency prior to surgery; (3) Malpositioning of the central venous catheter (4) History of alcohol abuse; (5) Pregnant; (6) Unwilling to provide consent.

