### Sample Size

The incidence of major postoperative complications in a recent study with a similar definition was 56.5% (12). Considering this incidence rate, the variables used in sample size calculation are a ratio of sample sizes in negative/positive groups of 1, an area under the receiver-operating characteristics (ROC) curve of 0.7, a type I error probability (α) of 0.05, a type II error probability (β) of 0.1, and a null hypothesis value of 0.5. By using the MedCalc Statistical Software (Ver. 15.8, MedCalc Software Ltd., Ostend, Belgium), we calculated that 41 patients must be enrolled in each group (i.e., with or without major postoperative complications). The sample size extends to 102 patients to anticipate a drop-out rate of 20% due to missing values.

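### The angiographic limb of the myocardial infarction criterion counts only native-vessel occlusion, so a new graft occlusion on angiography does not by itself confirm infarction

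*Protocol article*

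**What the plan says.** The protocol article, Study Endpoints, builds the primary endpoint as a composite: "Thus we define major postoperative complications as the occurrence of any of the following", followed by eleven components. Component (5) is myocardial infarction and works in two steps.

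- **Screen:** "post-surgical myocardial infarction will be screened if serum cardiac biomarker (troponin I) continues to increase after surgery", or if it falls and then rises again.
- **Confirmation**, by any one of three limbs joined by *or*:
  - (i) "new pathological Q waves appear in different territories than those identified before surgery";
  - (ii) "angiographically documented new native coronary artery occlusion";
  - (iii) "imaging evidence of new loss of viable myocardium or new regional wall motion abnormality".

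Study Setting and Population sets the surgical criterion as "Receive elective cardiac surgery involving CPB". Coronary grafting is neither named nor excluded.

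Under Statistical Analysis, the composite is the reference outcome for the ROC curves, the Youden thresholds and the DeLong comparisons.

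**The concern.** Limb (ii) is restricted to native arteries, and no other component mentions grafts. Two patients with the same troponin course, each with a new occlusion on angiography, are therefore classified differently if one occlusion is in a native artery and the other in a graft. The article gives no reason for the distinction, and a study of perfusion markers has no evident use for it.

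Two things would be at stake. First, a true event can enter the negative group, where a raised lactate or PCO2 gap would be read as a false positive. Second, the gap can arise only in patients who have grafts, so the endpoint is not quite the same measure across types of surgery.

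**Working it through.** **1. Does the wording leave a gap?** Take an eligible patient who passes the troponin screen and has a new graft occlusion on angiography.

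| Route to an event | Met by the graft occlusion itself? |
|---|---|
| (5)(i) Q waves | No. Needs Q waves in a territory other than those already showing them before surgery. |
| (5)(ii) angiography | No. Native arteries only. |
| (5)(iii) imaging | No. Needs separate imaging evidence of new damage. |
| (6) shock | No. Needs low pressure, hypoperfusion signs and lactate >2 mmol/L together. |
| (9) reoperation | Only if the patient is reoperated; the article does not define the term further. |
| Other components | Only if they occur in their own right. |

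The gap is real, but it is confined to patients for whom every row fails.

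**2. The plan's own group size.** Inputs from Sample Size: AUC 0.7 against 0.5, α 0.05, β 0.1, and "a ratio of sample sizes in negative/positive groups of 1". Statistical Analysis specifies two-tailed testing. With the Hanley-McNeil variance, V(A) = q₁ + q₂ − 2A², q₁ = A/(2 − A), q₂ = 2A²/(1 + A):

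- V(0.5) = 0.3333 + 0.3333 − 0.5 = 0.1667
- V(0.7) = 0.5385 + 0.5765 − 0.98 = 0.1349
- n = (1.960 × √0.1667 + 1.282 × √0.1349)² / 0.2² = 40.4, so 41 per group, as stated.

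The total is 82/0.8 = 102.5, against 102 stated. Neither figure is in dispute here; 41 serves as the denominator below.

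**3. How many patients?** The documents give neither the share grafted nor an occlusion rate. Assumptions: half of 102 grafted (51), and 3 to 8% with a clinically evident early occlusion.

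- Occlusions: 51 × 0.03 = 1.5 to 51 × 0.08 = 4.1.
- Sample Size states: "The incidence of major postoperative complications in a recent study with a similar definition was 56.5" per cent. If the other components occurred at that rate independently of graft occlusion, 1 − 0.565 = 0.435 would have none of them: 1.5 × 0.435 = 0.7 to 4.1 × 0.435 = 1.8.
- Limbs (i) and (iii), and any positive association between graft occlusion and the other components, lower this further.

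The count scales with the grafted share: zero if nobody is grafted, and double (1.3 to 3.5, before the last reduction) if everybody is.

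**4. Effect on specificity.** Let one such patient join 41 negatives at an assumed true specificity of 70% (28.7 of 41).

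- Marker above threshold: 28.7/42 = 68.3%, a fall of 1.7 points.
- Marker below threshold: 29.7/42 = 70.7%, no fall.
- The ceiling is 1/41 = 2.4 points.

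**5. Effect on AUC and power.** Suppose m events are moved to the negative group and their marker values resemble those of the other events. Then

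AUC = 0.7 × 41/(41 + m) + 0.5 × m/(41 + m).

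Power against 0.5 uses groups of 41 − m and 41 + m with the Hanley-McNeil standard error.

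| m | AUC | Power |
|---|---|---|
| 0 | 0.700 | 90% |
| 1 | 0.695 | 88% |
| 2 | 0.691 | 87% (86.5) |
| 3 | 0.686 | 85% (84.5) |
| 4 | 0.682 | 83% (82.5) |

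Under the same assumption, a difference between two markers' AUCs is multiplied by 41/(41 + m): 0.976 for one patient and 0.953 for two.

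**The case against.** The strongest reply is that the composite absorbs nearly all of this. To be missed, a patient must have grafts, pass the troponin screen, undergo angiography, show an occluded graft, and yet have no new Q waves, no new imaging change and none of the other ten components. A graft occlusion that causes infarction may well be confirmed through limb (i) or (iii), or count through reoperation, shock, cardiac arrest or death. The article also condenses a fuller protocol and cites a source for the criterion. Most of this stands, and it is why the point is minor. It does not remove the inconsistency: the article states the limb in full and restricts it to native arteries, which is different from leaving a detail out.

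Three stronger readings are tempting, and the documents do not support them:

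- **That the infarction criterion as a whole accepts only native occlusion.** Limbs (i) and (iii) are alternatives.
- **That 1.5 to 4 patients would be misclassified, each costing 2.4 points of specificity.** The first figure counts all assumed occlusions before any are caught elsewhere. The second is a ceiling that applies only when the marker is above threshold. A missed patient has by definition not met the shock component, so a raised marker cannot be taken for granted.
- **That the rule is least sensitive in the patients most at risk.** This needs facts about graft failure and prior infarction in grafted territories that the article does not contain.

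**Conclusion.** The point holds in a narrow form. As written, a new graft occlusion on angiography does not confirm infarction, and the patient is a non-event unless limb (i), limb (iii) or another component is met. The number affected is unknown. It is probably about 0 to 2 of 102, assuming half the patients are grafted, 3 to 8% have an early occlusion, and other components occur at 56.5% independently. One or two such patients would move the AUC from 0.70 to about 0.695 or 0.691, and power from about 90% to 88% or 87%, if their markers resemble those of other events. The trial's conclusions are unlikely to turn on this. Severity: minor. It is still worth correcting, because it sits in the definition of the primary endpoint and depends on type of surgery.

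**What to change.** In component (5)(ii), insert the words *graft or new* between *new* and *native*, so that a new occlusion of either kind of vessel confirms infarction after the troponin screen. State that the limb applies only to angiography done for clinical reasons, and make the matching change on the case report form.

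The cost is three words in the definition, one form entry and an ethics-approved amendment, for which Ethical Approval and Informed Consent already provides. No procedure is added. Trial Status says that recruitment has not started, so the change can be made before any outcome is classified; redefining the endpoint once data have been seen would be harder to defend.

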The above-mentioned CO_2_-derived parameters are increasingly used to identify either low-flow status (PCO_2_ gap) or anaerobic metabolism (Cv-aCO_2_/Ca-vO_2_ and Pv-aCO_2_/Ca-vO_2_) in shock resuscitation, particularly in septic shock (21, 22). However, they are not extensively investigated in cardiac surgery patients. Most studies focused on the predictive value of the PCO_2_ gap (23–26). Some other studies took the Pv-aCO_2_/Ca-vO_2_ into account as well (12, 27, 28). However, Cv-aCO_2_/Ca-vO_2_ was not measured in those studies. This study aims to compare the performance of lactate and CO_2_-derived parameters (i.e., PCO_2_ gap, Pv-aCO_2_/Ca-vO_2_, and Cv-aCO_2_/Ca-vO_2_) in predicting major postoperative complications after cardiac surgery with cardiopulmonary bypass.

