### CPB and Perioperative Management

The induction will consist of propofol, etomidate, or ketamine as appropriate. Patients will be intubated, and a central venous catheter will be placed *via* the internal jugular vein or subclavian vein. The initial tidal volume will be ~8 mL/kg, and the respiratory rate will be adjusted to maintain an arterial CO_2_ pressure (PaCO_2_) of 35–40 mmHg during the surgery. Sufentanil or remifentanil will be used for analgesia. The neuromuscular blockade will be induced by using rocuronium, cisatracurium or atracurium. Continuous administration of propofol or sevoflurane will be used for anesthesia maintenance. After attaining an activating clotting time (ACT) > 480 s *via* heparin administration, CPB will be initiated by using an occlusive roller pump (Jostra, Germany) and a membrane oxygenator (Affinity 7,000, USA). The pump flow will be around 2.0–2.6 L/min/m^2^ during CPB. The mean arterial pressure (MAP) will be maintained at 60–80 mmHg. Cephazolin will be administered as perioperative antibiotic prophylaxis. Patients will be transmitted to and monitored in the ICU after the surgery.

The postoperative ICU management will be as follows: fluid infusion (normal saline, Ringer's solution, or gelatin); red blood cells will be transfused to maintain hemoglobin concentration; fresh frozen plasma and platelets will be given when bleeding was suspected; vasopressors and inotropes will be continuously infused to achieve the hemodynamic targets: MAP ≥65 mmHg, urine output ≥0.5 mL/kg, cardiac index ≥2.5 L/min/m^2^ or a mixed venous saturation of >60%; analgesics will include sufentanil or remifentanil; sedation will consist of propofol or midazolam; ventilation will be continued until patients are awake, hemodynamic stable and with no bleeding, after that patients will be wean from the ventilator and extubated.

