### Data Collection and Follow-Up

Once admitted into ICU, demographic data, history of past illness, diagnosis, preoperative ejection fraction, and the New York Heart Association (NYHA) functional classification will be collected. The type of surgery, duration of operation, CPB and aortic clamping, intra-operative transfusion, net fluid balance, and the doses of vasopressors and inotropic agents during the operation will also be recorded. The sequential organ failure assessment score (SOFA) and Acute Physiology and Chronic Health Evaluation (APACHE) II score at enrollment and the daily highest score during the follow-up period will be recorded. Blood samples will be drawn *via* both arterial line and central venous catheter for blood gas analysis (GEM 3500, Instrumentation Laboratory Co., MA, USA) at ICU admission (T_0_), and 3 (T_3_), 6 (T_6_), and 12 h (T_12_) later. No personal information will be collected.

Patients will be followed up for 28 days. The occurrence of major postoperative complications (see below) will be recorded. The duration of mechanical ventilation and length of ICU stay will also be recorded. Daily fluid balance and the highest vasoactive-inotropic score (VIS) will be calculated. VIS will be calculated as dopamine dose (μg/kg/min) + dobutamine dose (μg/kg/min) + 100 × epinephrine dose (μg/kg/min) + 100 × norepinephrine dose (μg/kg/min) + 15 × milrinone dose (μg/kg/min) + 10,000 × vasopressin dose (U/kg/min) (30).

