### Statistical Analysis

EpiData (ver. 3.1, Denmark) will be used for data entry and data quality control. Multiple imputations will be used to handle missing data. Perioperative characteristics will be compared according to the occurrence or not of major postoperative complications. Continuous variables will be assessed for normal distribution and presented as means and standard deviations or medians and inter-quartile ranges as appropriate; the inter-group comparison will be performed by using Student's *t*-test for normally distributed variables or Mann-Whitney *U*-test for non-normally distributed variables. Categorical variables will be presented as numbers and percentages and analyzed by using χ^2^-test or Fisher's exact tests as appropriate. Ordinal variables will be analyzed by using the rank-sum test.

ROC curve analysis will be carried out to assess the predictive performance of lactate and CO_2_-derived parameters. The optimal thresholds for predicting major postoperative complications will be determined by maximizing the Youden index. Sensitivity, specificity, predictive values, and likelihood ratios will be calculated. The performance of the ROC curves will be compared by using DeLong's method (41). A *p* < 0.05 (two-tailed) will be considered significant. Analyses will be performed by using SPSS Statistical Software (Ver. 23.0, IBM Co., NY, USA) and MedCalc Statistical Software (for the comparison of ROC curves).

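### Lactate is both an index test and a required criterion of the shock component, so its comparison with the CO2-derived parameters leans towards lactate by an amount the protocol does not determine

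*Protocol article*

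**What the plan says.** - **Aim (Background).** "This study aims to compare the performance of lactate and CO_2_-derived parameters" in predicting major complications after cardiac surgery with bypass.
- **Analysis (Statistical Analysis).** "ROC curve analysis will be carried out to assess the predictive performance of lactate and CO_2_-derived parameters". The curves are then compared by DeLong's method at a two-sided 0.05 level, and thresholds are chosen by the Youden index.
- **Endpoint (Study Endpoints).** "Thus we define major postoperative complications as the occurrence of any of the following", followed by eleven components. Component 6, shock, has three criteria joined by 'and': a pressure criterion, then "clinical signs of tissue hypoperfusion, and iii) serum lactate >2 mmol/L (39").
- **Timing (Data Collection and Follow-Up).** Index blood is drawn "at ICU admission (T_0_), and 3 (T_3_), 6 (T_6_), and 12 h (T_12_) later". For outcomes, "Patients will be followed up for 28 days". The text does not say that only complications after the index sample count, that shock present on ICU admission is excluded, or that the shock lactate is a separate measurement.
- **Limitations (Discussion).** Three are listed. This overlap is not among them.

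**The concern.** A head-to-head comparison of predictors is fair only if the outcome is settled without reference to any of them, or with equal reference to all. Here one of the four index tests is written into the outcome and the other three are not. This is incorporation bias on one side of the comparison.

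The study's main question is which marker predicts better. An overlap that raises lactate's AUC could hide a real advantage of a CO2-derived parameter, or show lactate as better when the two are equal. It also affects lactate's Youden threshold, sensitivity and predictive values. A larger sample would not remove it.

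**Working it through.** **1. Where lactate decides the outcome.** Let D be any component other than shock, and H the pressure and hypoperfusion criteria both met. A patient is a case if D, or if H and lactate >2 mmol/L.

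| D | H | Case status |
|---|---|---|
| yes | either | case, whatever the lactate |
| no | no | non-case, whatever the lactate |
| no | yes | case only if lactate >2 mmol/L |

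The bias arises only in the third row. Its direction follows from the definition. Its size depends on how many patients fall in that row and how closely the shock lactate follows the index lactate. The document gives neither.

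**2. The plan's own figure.** Sample Size uses AUC 0.7 against 0.5, α 0.05, β 0.1 and ratio 1. With V(A) = A/(2−A) + 2A²/(1+A) − 2A², V(0.5) = 0.1667 and V(0.7) = 0.1349. Then n = (1.96√0.1667 + 1.2816√0.1349)² / 0.2² = 40.4, so 41 per group as stated. 82/0.8 = 102.5, against 102 stated. The overlap does not affect this figure, which concerns a single AUC.

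**3. Same lactate value in both roles (all inputs assumed).** D occurs in 50%. H occurs in 20–60% and is unrelated to the markers. Lactate and one CO2 marker are equally accurate for D (AUC 0.65–0.70). Lactate exceeds 2 in 15% or 30%; Background gives hyperlactatemia of about 10–20%, without a cut-off. Spurious AUC gain for lactate, by simulation:

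| Marker correlation given D | Lactate >2 in 15% | Lactate >2 in 30% |
|---|---|---|
| 0 | 0.013–0.054 | 0.030–0.102 |
| 0.5 | 0.007–0.026 | 0.016–0.054 |

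**4. Index and shock lactates allowed to differ (all inputs assumed).** D and H each raise both markers equally (AUC 0.7 each). H occurs in 20–40% and D in 40–45%. Median lactate is 1.5 or 2.0 mmol/L and marker correlation is 0.3. These six scenarios give a composite prevalence of about 51–58%, against the 56.5% in Sample Size. The last column is the share of trials with n = 82 in which DeLong's test wrongly favours lactate (nominal 2.5%).

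| Correlation of the two lactates given severity | Spurious gain | Wrongly favours lactate |
|---|---|---|
| 1 (same value) | 0.029–0.079 | 5.8–23.7% |
| 0.6 | 0.015–0.044 | 4.3–9.3% |
| 0.3 | 0.008–0.021 | 3.4–4.6% |
| 0 | about 0 | 2.4–2.9% |

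**5. Effect on power.** 0.565 × 82 = 46 cases, leaving 36 non-cases. Hanley–McNeil standard errors are 0.0572 (AUC 0.70) and 0.0482 (AUC 0.80). With correlation 0.5 the standard error of the difference is √(0.0572² + 0.0482² − 2×0.5×0.0572×0.0482) = 0.0533. For a true CO2 advantage of 0.10, power = Φ(0.10/0.0533 − 1.96) = 47%. If a gain of 0.05 leaves 0.70 against 0.75, the standard error is 0.0553 and power = Φ(0.05/0.0553 − 1.96) = 15%. Gains of 0.01–0.026 leave roughly 27–40%.

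**6. Without component 6.** The outcome becomes D alone. In both models the two markers then have the same distribution given the outcome, so the difference is zero by construction. A rerun of both models gave differences within 0.001 of zero.

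**The case against.** The strongest reply is that the effect may be small.

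- **Dilution.** Shock is one of eleven components, and several others, such as a PaO2/FiO2 below 300 mm Hg or delirium, may be frequent. In the first model with lactate >2 in 15%, shock-only cases were about 1–3% of patients, or one to three of 102.
- **Timing.** Index samples end at 12 hours and follow-up runs to 28 days, so later shock would rest on a different lactate.
- **Extreme inputs.** The upper figures need hypotension with hypoperfusion signs in 60% of elective patients, unrelated to either marker. Background describes the PCO2 gap as an index of the adequacy of cardiac output, which makes that independence doubtful.

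All of this stands as a limit on size. None of it removes the overlap or changes its direction, and the protocol contains no rule that would ensure the favourable case.

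Three stronger readings are tempting and are not supported:

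- **That a high lactate by itself creates an event.** It does so only when the pressure and hypoperfusion criteria are also met.
- **That the pressure figures contradict each other.** The ICU "hemodynamic targets: MAP ≥65 mmHg" is a treatment target. The limit in "systolic arterial pressure <90 mm Hg or the mean arterial pressure <70 mm Hg" is one criterion of a diagnosis that also needs hypoperfusion signs and lactate. They serve different purposes, and the point does not depend on them.
- **That power falls from 47% to 15%.** That requires a gain of 0.05. At marker correlation 0.5, this gain is not reached with lactate >2 in 15% of patients, and is reached only near the top of the range with 30%.

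**Conclusion.** The concern holds as a one-sided incorporation bias in the main comparison. It should be fixed. The text alone establishes the overlap and its direction.

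The size is unknown. It is about 0 if the shock lactate is unrelated to the index lactate given severity, or if few patients qualify by shock alone. It is about 0.01–0.05 in AUC if the same value serves both roles, the markers correlate 0.5 and hypotension with signs occurs in 20–60%. It is about 0.10 in a worst case, with markers independent given the other components, lactate >2 in 30% and hypotension with signs in 60%.

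A reader might infer that lactate's result will be seriously inflated. The documents do not support this, because every input that sets the size is an assumption. The stated sample size is not in question.

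**What to change.** 1. In Statistical Analysis, specify that the DeLong comparisons of lactate with the CO2-derived parameters use the composite without component 6. Patients with shock and any other component remain cases.
2. Report the same comparisons on the full composite alongside, so the influence of the overlap can be seen.
3. Keep the full composite as the primary endpoint for all other purposes.
4. Record each component and its time of onset. Data Collection and Follow-Up says only that the occurrence of major complications will be recorded, so separate recording cannot be assumed.
5. Add the overlap to the limitations.

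**Why not delete only the lactate criterion?** That would also remove the overlap. But removing a required criterion adds events, and would count as shock every patient with low pressure and hypoperfusion signs.

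**Cost.** Wording and some case report form fields. Trial Status says recruitment has not started, so the choice can still be made before any data are seen. The downside is that shock-only cases become non-cases in this comparison, which then departs slightly from the stated endpoint. Their number is probably small but unknown: one to three of 102 in the first model at 15%. One scenario of the second model, where 16% of cases qualified by shock alone at 53% prevalence, gives 0.16 × 0.53 × 102, or about nine.
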